### Sample size

Random variation in choices can be expected to be smaller the better risk information is understood. So we will expect a stronger association (larger R2) between the expected utility model (A) and what participants decide (D) the better the information about the risk of heart disease is understood. Turning this around, a significantly stronger association between the model and what participants decide for one presentation (G1) compared with another (G2) suggests that the first presentation was better understood than the second.

The detectability of a difference in magnitude between population R’s is not a simple function of the difference.10 That is, if we were to define j = R1 – R2 and try to use j as the effect size, the detectability of j under fixed conditions of  (level of significance) and sample size n, is not constant, but depends on where along the R scale the difference j occurs. The Fisher Z transformation of R provides a solution to this, and the effect size index q = Z1 – Z2 gives values whose detectability does not depend on whether the Z’s are both small or both large. Cohen considers q = 0.10 as a small effect size, and the following pairs of R’s illustrate this amount of difference: (0.00;0.10), (0.20; 0.29), (0.40; 0.48), (0.60; 0.66), (0.80,0.83), (0.90;0.92), (0.95;0.96). A medium effect size is q = 0.30 and the following pairs of R’s illustrate this amount of difference: (0.00;0.29), (0.20; 0.46), (0.40; 0.62), (0.60; 0.76), (0.80,0.89), (0.90;0.94), (0.95;0.97). A large effect size is when q = 0.50. This is illustrated by the following pairs of R’s: (0.00;0.46), (0.20; 0.61), (0.40; 0.73), (0.60; 0.83), (0.80,0.92), (0.90;0.96), (0.95;0.98).

As we have no prior information about the size of R within any of the information groups, we will conduct a pilot study. The number of subjects to be included in each group in the pilot study is based on power calculations for detecting a medium and a somewhat larger effect size (assuming equal size of the groups):

| q |  (2-sided test) | Power | N |
| --- | --- | --- | --- |
| 0.30 | 0.05 | 0.70 | 140 |
|  |  | 0.75 | 157 |
|  |  | 0.80 | 177 |
|  | 0.10 | 0.70 | 108 |
|  |  | 0.75 | 123 |
|  |  | 0.80 | 140 |
| 0.40 | 0.05 | 0.70 | 80 |
|  |  | 0.75 | 90 |
|  |  | 0.80 | 101 |
|  | 0.10 | 0.70 | 62 |
|  |  | 0.75 | 70 |
|  |  | 0.80 | 80 |

As can be seen from the table above, the required sample size varies from 80 to 140 per group. However, if we manage to recruit a minimum of 100 subjects into each group, we are likely to obtain estimates for the difference in R’s in addition to estimates of the R for each group.

The total sample size that is needed will be calculated based on the results of the pilot study. Because we are not certain how best to analyse the data, we will also explore alternative ways of analysing the results (see Attachment 2) and, if needed, adjust the sample size calculations to take account of this.

### Descriptive statistics

The results will be summarised in tables by means, standard deviations, counts and percentages as appropriate for the each variable for each (presentation) group of participants and for all participants. Density distributions will be used to present the VAS results, which are continuous. Bar charts will be used to present the LTRS results, which are categorical. Graphical displays will also be used to compare the VAS and LTRS results.

### Secondary comparisons

Because participants will only be recruited from the general public in the USA for the pilot, it will be possible to compare the use of VAS’s and LTRS’s, but not to conduct the other secondary comparisons with data from the pilot study. The analysis comparing the use of VAS’s to LTRS’s will be similar to the analysis comparing different presentations. We expect a stronger association (larger R2) between the expected utility model (A) and what participants decide (D) the better the way of eliciting the relative importance of the consequences of starting statins gives values that are congruent with the participants true values. Turning this around, a significantly stronger association between the model and what participants decide for one way of eliciting values (VAS’s) compared with the other (LTRS’s) would suggest that the first way was better than the second.

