## METHODS

### Study design

The study is a Web-based randomized trial in which participants will be randomized to one of six ways of presenting information about CVD risk reduction listed above. The relative importance of the consequences of starting statins will be elicited in two ways (VAS’s and LTRS’s) for all of the participants. The order in which this is done will be randomized.

A printout of the Webpages that will be used is attached [Available as a supporting PowerPoint file, Figure S3.1 Facimile HIPPO Webpages for protocol]. Upon logging into the study Website, participants will be given information about the study and asked to give informed consent to participate. They will be presented with a brief scenario in which they are asked to imagine that they have elevated cholesterol and are given the option of taking pills that lower cholesterol (statins). The relative importance of CVD risk reduction, taking pills and costs will be elicited using VAS’s and LTRS’s. They will then be presented with information about the effect of statins on the risk of heart disease, using one of the presentations listed above, the need to take a pill each day and the out-of-pocket costs; and asked whether they would decide to take the pills or not. Baseline risk will then be altered in the direction that shifts the expected utilities towards the opposite decision; i.e. the baseline risk will be increased for respondents who decide not to take the pills and decreased for those who decide to take the pills. Participants will then be asked what they would decide again. After this they will be asked questions about their decision and about themselves and, finally, they will be asked which of the six ways of presenting CVD risk reduction they would prefer.

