### Analysis

We have the following variables:

UCVD = utility of having heart disease; i.e. 1 – how difficult it would be to have cardiovascular (“heart”) disease on a scale from 0 to 1; 1 equals the most difficult

UPill = utility of having to take a pill each day; i.e 1 – how difficult it would be to have to take a pill each day on a scale from 0 to 1; 1 equals the most difficult

UCost = utility of not having to pay for pills; i.e. 1 – how difficult it would be to have to pay an additional amount of money each month for equivalent to the out-of-pocket cost of taking a statin on a scale from 0 to 1; 1 equals the most difficult

PP = probability of having heart disease with taking pills

PN = probability of having heart disease without taking pills

Using these variables we can calculate the expected utility (EU) for a decision to take pills:

EU(taking pills) = PPּUCVD + (1 - PP)ּ(1-UCVD) – (1-UPill) – (1-UCost)

Operationally this transforms to:

EU(taking pills) = PPּ(1-VAS_hrt) + (1 - PP)ּ(VAS_hrt) – (VAS_pill) – (VAS_cost)

or not to take pills:

EU(not taking pills) = PNּUCVD + (1 - PN) ּ (1-UCVD)

Operationally this transforms to:

EU(not taking pills )= PNּ(1-VAS_hrt) + (1 - PN)ּ(VAS_hrt)

and the difference between these (A):
A = EU(taking pills) – EU(not taking pills)

The difference in expected utilities can range from positive values (in favour of taking pills) to negative values (in favour of not taking pills).

If G is used to represent the presentation group to which a participant is randomised and D represents the decision to take pills or not, then the relationship between D and A can be modelled as follows:

(Eq 1)          logit(D) = 0 + 1A

To examine the relationship between the model of what participants might be expected to decide based on the expected utilities of the two options (Eq 1) with how the information was presented, Eq 1 will be fit for each group G. We will then compare the fit between different groups by comparing the R2 between the different groups.

Using a maximum-likelihood model will allow us to adjust for other factors (age, gender, profession) in a natural way. This allows us to test for differences in professional background (scientists or engineers vs GPs or other health professionals vs others), and differences across countries (Canada vs Germany vs Norway vs USA). To the extent that any of these factors are confounders, adjusting for these factors would improve the precision of our model.

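### VAS and LTRS are completed by the same participants, but their comparison is modelled on one between independent randomised groups, which would be conservative if the two scores are positively correlated

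*Protocol*

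**What the plan says.** Study design (Protocol) has the relative importance of the consequences elicited by both methods "for all of the participants. The order in which this is done will be randomized". The method is therefore a within-participant factor, and only its order is allocated at random.

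Secondary comparisons says that the VAS–LTRS analysis "will be similar to the analysis comparing different presentations". Its criterion is "a significantly stronger association between the model and what participants decide for one way of eliciting values" than for the other, so a significance test is intended.

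The analysis referred to is in the Analysis section. Eq 1, the logistic model of decision D on expected-utility difference A, is fitted in each presentation group, and then: "We will then compare the fit between different groups by comparing the R2 between the different groups". Those groups are separate people, since "participants will be randomized to one of six ways of presenting information about CVD risk reduction".

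The only statement of precision is under Sample size. It works on the difference q between two Fisher Z values ("The Fisher Z transformation of R provides a solution to this"), "assuming equal size of the groups".

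No section mentions pairing, the shared decision D, or the correlation between the two versions of A. Attachment 1 (Alternative analyses) adds only that other ways of analysing VAS versus LTRS will be examined.

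**The concern.** For two presentation groups, the two R's come from different people and their sampling errors are independent. For VAS and LTRS, the same person supplies both values of A, and both are related to the same D. The two R's then tend to rise and fall together from sample to sample, and the variance of their difference shrinks by a covariance term. A method built for independent groups leaves that term out.

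The comparison is a stated additional objective, and Secondary comparisons describes it as the one secondary question that the pilot can address. The pilot is also meant to guide the methods of later HIPPO studies. An inflated standard error could hide a modest advantage of one elicitation method when that choice is being made.

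**Working it through.** **1. Reproduce the plan's own table.** With independent groups, Var(Z1 − Z2) = 2/(N − 3), so N per group = 2·[(z for two-sided alpha + z for power)/q]² + 3.

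- q = 0.30, alpha 0.05, power 0.70: 2·[(1.960 + 0.524)/0.30]² + 3 = 140.2. The table row reads "0.30 | 0.05 | 0.70 | 140".
- q = 0.30, alpha 0.05, power 0.80: 2·[(1.960 + 0.842)/0.30]² + 3 = 177.4 (table: 177).
- q = 0.40, alpha 0.05, power 0.80: 101.1 (table: 101).

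All 12 cells reproduce in this way, so the stated precision model is the independent-groups one.

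**2. Variance when both R's come from the same people.** For two correlations that share one variable (D), with common value R and correlation ρ between the VAS-based and LTRS-based A:

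- ψ = ρ(1 − 2R²) − ½R²(1 − 2R² − ρ²)
- c = ψ/(1 − R²)²
- Var(Z1 − Z2) = 2(1 − c)/(N − 3)
- independent SE divided by paired SE = 1/√(1 − c)

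Example with R = 0.30 and ρ = 0.7: ψ = 0.7 × 0.82 − 0.045 × (0.82 − 0.49) = 0.574 − 0.015 = 0.559; c = 0.559/0.8281 = 0.675; ratio = 1/√0.325 = 1.75.

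**3. Range.** The Protocol says there is no prior information on R and gives no ρ. Both are assumptions here.

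| ρ | SE ratio, R = 0 to 0.6 | SE ratio, R = 0.30 |
|---|---|---|
| 0 | 0.94–1.00 | 0.98 |
| 0.3 | 1.07–1.20 | 1.16 |
| 0.5 | 1.22–1.41 | 1.37 |
| 0.7 | 1.53–1.83 | 1.75 |
| 0.8 | 1.84–2.24 | 2.14 |

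**4. Check on the logistic scale.** The formula treats R as a product-moment correlation, whereas Eq 1 is logistic with a binary D. A simulation of McFadden R2 from logistic fits (N = 600, 1,500 replicates per setting) gave ratios of 1.16, 1.30, 1.64 and 2.04 at ρ = 0.3, 0.5, 0.7 and 0.8. These are close to the formula.

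**5. Effect on size and power.** Sample size section: at least 100 in each of six groups, so N = 600 if the groups are pooled (an assumption). Independent SE = √(2/597) = 0.0579, giving a rejection threshold of 1.96 × 0.0579 = 0.113. With R = 0.30:

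- ρ = 0.7: paired SE = 0.0579 × √0.325 = 0.0330. At a true q of 0.10, the independent-SE test rejects with probability Φ((0.10 − 0.113)/0.0330) = 34%; the paired test with Φ(0.10/0.0330 − 1.96) = 86%. The actual size of the nominal 5% test is 2Φ(−1.96 × 1.75), about 0.06%.
- ρ = 0.5: paired SE = 0.0424; 38% against 66%; actual size 0.7%.
- ρ = 0.3: paired SE = 0.0499; 39% against 52%; actual size 2.3%.

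For larger differences the loss fades. At ρ = 0.7 the independent-SE test rejects 87% of the time at q = 0.15, 99.6% at q = 0.20, and practically always at q = 0.30.

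**The case against.** The strongest reply is that the defect is inferred. Secondary comparisons calls the analysis similar, not identical, and names no test, standard error or interval. The Fisher Z variance appears only in the sizing of the presentation groups. The method is also left partly open: finding the best analysis is an aim of the pilot, the Sample size section admits uncertainty about it, and Attachment 1 promises alternatives for VAS versus LTRS. A statistical analysis plan that is not shown could specify a paired method. All of this stands, and it limits the point to what follows if the comparison is carried over as described. It does not remove the point. The Protocol does more than stay silent: it names a between-group comparison as the model for a within-participant question.

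Two stronger readings are tempting. One is that the error bars will be far too wide. The documents give no error bars for this comparison and no VAS–LTRS correlation; the excess is about 7–41% at correlations of 0.3–0.5 and reaches roughly double only near 0.8. The other is that a real difference will usually be missed. That applies to q = 0.10, which the Protocol itself calls small. At q = 0.15 and R = 0.30, the independent-SE test still rejects about 77% of the time or more at correlations of 0.3–0.7, and the Protocol's own table uses q = 0.30 and 0.40.

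It is also fair that the error is conservative for positively correlated scores, so it would not create a false claim for either method, and that the primary objective is untouched. Randomised order already balances carry-over, so its absence from the stated analysis is not a fault.

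**Conclusion.** The point holds in a limited form. The design is paired, while the analysis it is modelled on, and the only precision model stated, are for independent groups. Followed as written, the VAS–LTRS comparison would be conservative, with a loss of power that is material for small differences and negligible at the effect sizes in the sample-size table when about 600 participants are pooled.

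The size rests on an assumed R (0 to 0.6) and an assumed correlation between the two expected-utility differences. The direction needs that correlation to be clearly positive. This is plausible for two ratings of the same three consequences by one person in one session, but the documents do not show it; at zero correlation there is no widening. The pilot can estimate both quantities.

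**What to change.** In Secondary comparisons, state that VAS and LTRS are compared within participants: fit Eq 1 with each version of A in the same people, take the difference in logistic R2, and give a confidence interval from a bootstrap that resamples whole participants. A test for dependent overlapping correlations (Steiger or Williams) can serve as an approximation only, because it is built for product-moment correlations and not for a logistic R2.

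A supporting comparison by elicitation order, or of the first-elicited method only, is optional. The latter uses about half the sample for each method and is then a comparison between groups.

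The cost is a sentence or two of wording and a little more analysis work. No extra data are needed.

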#### ETHICS

The interventions in this study, alternative ways of presenting information on risk reduction, and asking the participants to make a hypothetical decision, are non-invasive and harmless. The same information presented in this study is widely available and is presented in many different ways, including those used in this study.10

Participants are informed on the consent screen that they can leave the study at any time, and they are given the option of having any data that they might have entered deleted.

Confidentiality of data entered by participants is ensured by not collecting any information that would make it possible to identify the participants. If participants fill out a form to request a report of the study results or they choose to participate in the lottery for a $100 gift certificate, their email or postal addresses will not be stored in the same database as their responses to the study questions.

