### Inclusion criteria

To be included in the trial participants must be > 18 years old and literate in one of the following languages English, French, German, Norwegian.

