### Recruitment

Participants will be recruited in the following ways:

- Invitations to participate will be sent to individuals by email in the US. The email addresses will be obtained through a vendor who has enlisted opt-in respondents for issues regarding health.
- Patients at a participating research facility will be given the opportunity to participate.
- Three additional means of recruiting participants will be used to assess the potential to recruit participants without sending out invitations by email and to compare the extent to which there are differences in results between participants recruited in these different ways:
  - Links to the study Website will be added to various Web pages that provide health information.
  - Internet surfers who come across the HIPPO Website will be invited to participate.
  - People will be approached in public areas, such as a shopping mall, and invited to participate using a computer that will be provided and with assistance, if it is needed.
- GPs will be contacted through Internet discussion groups or by email and invited to participate.

Potential participants will be offered options to participate in a lottery for a $100 gift certificate and to receive a report of the results of the study.

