### Allocation

Allocation to one of the six presentations will be determined by block-randomization. We have created a sequence of 600 presentation assignments by generating 100 blocks of the 6 presentations using [http://www.randomization.com](http://www.randomization.com/) (Randomization plan created on 17 April 2002, 16:03:41. To reproduce this plan use the seed 11049). This sequence will be looped and repeated until an adequate sample size is achieved.

The order in which we elicit the relative importance of the consequences of starting statins, VAS’s versus LTRS’s) will also be allocated by block-randomization.

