### Data collection

Participants will enter responses directly by responding to the questions on the HIPPO website. The data generated will be stored anonymously in a database. Only completed records will be used in the main analyses.

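### The protocol describes no safeguard against the same person taking part twice, and repeat records could not be removed later without a non-identifying marker

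*Protocol*

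**What the plan says.** Protocol, Recruitment, lists several routes. Two of them need no individual approach: "Links to the study Website will be added to various Web pages that provide health information", and "Internet surfers who come across the HIPPO Website will be invited to participate". The same section offers an incentive and states no limit of one entry per person: "Potential participants will be offered options to participate in a lottery for a $100 gift certificate".

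Protocol, Inclusion criteria, has only an age and a language condition: "To be included in the trial participants must be > 18 years old and literate in one of the following languages". First participation is not a condition.

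Protocol, Study design, describes two hypothetical decisions at two baseline risks and some questions, after which "finally, they will be asked which of the six ways of presenting CVD risk reduction they would prefer". Protocol, Allocation, uses a list of 600 assignments in blocks of six: "This sequence will be looped and repeated until an adequate sample size is achieved".

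On identification, Data collection says: "The data generated will be stored anonymously in a database". It then limits the main analyses to completed records, with no rule on duplicates. ETHICS adds: "Confidentiality of data entered by participants is ensured by not collecting any information that would make it possible to identify the participants". Addresses given for the lottery or the results report are kept in a separate database from the responses.

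**The concern.** The trial compares the effect of seeing one presentation with the effect of seeing another. A person who has reached the last page has met all six and has already decided at two baseline risks. A second record from that person no longer measures the effect of one presentation on an unexposed reader, yet nothing in the text shown keeps it out of the main analyses or marks it.

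This cannot be left to a later analysis plan, which can work only with fields that were collected. As described, the response database holds nothing by which a repeat could be recognised. Duplicate lottery addresses might be noticed, but they could not be linked to responses.

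Two planned uses of the data add to the stake. The main sample size is to be set from the pilot results, so a diluted pilot difference would carry into that calculation. Recruitment also intends to compare results between routes. Repeat entry is probably easiest on the open Web routes and could then be mistaken for a difference between routes.

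**Working it through.** **Inputs.** From Protocol, Sample size: q = 0.30, two-sided alpha 0.05, power 0.80, N = 177 per group. From Allocation: six arms in equal blocks. Not in the documents: the share r of records that are repeats, here assumed to be 2% to 10%.

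**1. The plan's own figure.** For two independent correlations on the Fisher z scale, n per group = 2 × ((z for alpha + z for power) / q)² + 3. With 1.960 + 0.842 = 2.802 and q = 0.30 this gives 177.4, against the stated 177. All twelve rows of the table reproduce to within one subject. No stated figure is wrong, but the formula assumes that each record is a separate, independent person.

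**2. Where a repeat lands.** If a returning person is allocated again among six equally likely arms, the chance of a different arm is 1 − 1/6 = 5/6 = 0.83. Within the same block of six it is certain.

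**3. Dilution.** Suppose a share r of the records in each arm are repeats by earlier completers, and that these carry no difference between presentations. The detectable difference then shrinks to about q′ = (1 − r) × q. Power is Φ(q′ / √(2/(n − 3)) − 1.960), and √(2/174) = 0.1072.

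| r (assumed) | q′ | q′ / 0.1072 − 1.960 | Power | N per group for 80% |
| --- | --- | --- | --- | --- |
| 0 | 0.300 | 0.838 | 0.80 | 177 |
| 2% | 0.294 | 0.782 | 0.78 | 185 |
| 10% | 0.270 | 0.558 | 0.71 | 219 |

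The last column uses the formula in step 1 with q′ in place of q (184.6 and 218.3, rounded up). In a pilot group of 100, the same range means 2 to 10 cross-exposed records.

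**4. Standard errors.** Two records from one person are positively correlated. Standard errors that count every record as a separate person are therefore too small for any estimate that contains both. This applies to an arm's own R when both records fell in that arm, and more so to figures pooled over all participants and to the VAS versus LTRS comparison. In a contrast of two arms, pairs split between those arms pull the other way, so no figure is put on this part.

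**5. Balance.** A returning person who is allocated again is allocated at random. Repeats therefore fall evenly on the arms in expectation and do not unbalance them.

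**The case against.** The strongest reply is that this rests on silence in a text from which relevant pages are missing. Study design refers to an attached printout of the Web pages, and ETHICS refers to a consent screen. Neither is shown, and either could hold an instruction to take part once or a technical check. Study design also speaks of logging in, which leaves access control open. This stands: the supportable statement is that no safeguard is described, not that none exists.

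Other limits stand too, and each blocks a stronger reading that a reader might infer:

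- **Every login is a new randomisation.** Allocation does not say so. It says only that the list is looped. The 5/6 holds on the condition that a returner is treated as new.
- **The lottery pays people to complete again.** It is optional, and the text does not tie entry to completion or say that repeat completion earns further entries.
- **The whole trial is open.** Emailed invitees, patients at the research facility and people helped in public areas are approached individually, although no single-use code is described for any route.
- **The confidentiality sentence is an error.** It excludes identifying information only. A random token, a cookie or a question on earlier participation is compatible with it, so the gap can be closed before launch.
- **Visitors abandon sessions until they get an arm they like.** Such a person need not have reached the page with all six presentations. Completion that depends on the arm is a separate matter of analysing completers only, and it exists without repeat entry.

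It can also be said that restricting analysis to first entries is a rule for an analysis plan. The rule may be, but the marker it needs must be built into data collection.

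**Conclusion.** The point holds in a limited form. In the text shown, open Web entry, eligibility by age and language alone, a final page covering all six presentations, anonymous storage and a main analysis set of all completed records together mean that a repeat completer would be counted as a new, unexposed participant and could not be found afterwards. The main expected effect is dilution of differences between presentations, with understated standard errors as set out in the working.

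The size is conditional. At an assumed 2% to 10% repeats, power falls from 0.80 to about 0.78 to 0.71 for q = 0.30 and 177 per group. This assumes that every repeat comes from an earlier completer, is treated as new and carries no presentation effect. The documents do not give the repeat rate, so they do not support reading this as certain or large contamination, as contamination that nothing could repair, or as a source of bias through unequal arms. It should be settled before launch, because a marker cannot be added to records already collected.

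**What to change.** First check the Web pages and the consent screen. Unless they already cover this:

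- Add to Inclusion criteria that the participant has not previously completed this study.
- Ask on the consent screen whether the person has taken part before, and store the answer with the responses.
- Set a random, non-identifying token or cookie that returns a revisitor to the original arm, and use single-use links for emailed invitations.
- State in Data collection and Analysis that comparisons between presentations use first entries only.

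None of this requires information that identifies anyone, so the commitment in ETHICS is kept. The cost is minor programming, one eligibility line, one question and one analysis-set line. The downside is that a few genuine first-time users of shared computers could be blocked or excluded. This includes the study's own computer in public areas, unless it is exempted from the cookie. A cookie can be cleared and a self-report can be false, so repeats would be reduced rather than ruled out.
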